## Methods

### Study Design

The study design has been primarily defined to address the primary aim of the study on the effectiveness of a 16-week MEP. For this reason, we will perform a multicenter randomized controlled trial with baseline and postassessments and an allocation ratio of 2:1 for intervention (IG) and control group (CG), respectively. Ethical approval has been obtained from the ethics commission of the Karlsruhe Institute of Technology. The study is retrospectively registered in the German National Register of Clinical Trials [DRKS00010538]. This study protocol considers guidelines and recommendations of the Standard Protocol Items: Recommendations for Interventional Trials (SPIRIT) [40,41] and Consolidated Standards of Reporting Trials (CONSORT) statements [42-44].

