### Sample Size

The required sample size was calculated via G*Power version 3.1.9.2 (Heinrich Heine University of Dusseldorf) [73], taking into account the following parameters: analysis of variance (ANOVA) for repeated measures, within-between interaction, small effect size (ɳ²=0.01, d=0.2) [74], 2-sided α-error of .05, power of .80 (1-β), and 2 groups and 2 measurements. The small effect size used for the calculation of required sample size is based on literature review and assumptions of relevant changes for IWD. Previous studies have reported high variation in the effect sizes of the primary outcomes balance, mobility, and gait. In their review, Blankevoort et al [22] reported small negative to large positive effect sizes for balance (d=–0.24 to d=3.59) and functional mobility (d=–0.25 to d=2.37) as well as no to medium effect sizes for normal gait speed (d=–0.11 to d=0.50). These reported variations do not allow determining actual effect sizes. Thus, the magnitude of relevant changes has to be considered to further support the selection of a small effect size. Because dementia is characterized by rapid progression linked to multiple impairments, it is assumed that even small effects are relevant. The calculation of sample size results in a required sample size of 100 participants for each group (total sample size of 200 participants). Considering reasons for dropout, the sample is set to 405 participants.

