### Dropout

We assume 3 reasons for dropout: (1) withdrawal from the study, (2) missing data, and (3) low attendance or adherence to MEP. Possible reasons for withdrawal are death, hospitalization, serious deterioration in state of health, refusal to participate, etc. Based on the literature review of Blankevoort et al [22], a dropout rate of 20% caused by withdrawal is expected. Missing data occur if participants are not able to complete the entire test battery because of motivational aspects or multiple motor and cognitive impairments. In addition, some participants will not participate at all in postassessments because of illness or other appointments. We assume a missing data rate of 15%. A total target number of 200 participants (100 per group) for the analysis and an assumed dropout rate (withdrawal and missing data) of 35% requires enrolling 270 participants into the study. Unfortunately, attendance and adherence are often not stated in previous studies [26]. Hence, we decided to double the sample of IG to ensure the required sample of 100 participants in this group. Low attendance and adherence may be caused by illness, motivation, other appointments, disinterest, or other reasons. Hence, a total sample size of 405 participants is required.

All participants will be asked at least twice if they are willing to participate in the assessments to reduce missing data. A familiar caregiver is asked to invite the participant if appropriate. If participants are not willing to complete all measures they are offered to choose assessments they are willing to complete. Moreover, all possible participants will be included in the data collection regardless of whether they discontinued or deviate from the intervention protocol. Caregivers will be asked to support the participants to get to training sessions to improve attendance. If participants miss a session, they are personally invited to the next training session.

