### Statistical Analysis

All statistical analysis will be done with SPSS version 23 (IBM Corp). Trained and experienced investigators will evaluate and enter data. Investigators evaluating and entering data are not the same as investigators assessing outcomes. The number of investigators is limited to 2 per assessment method. Prior to actual analysis, interrater reliability (Cohen kappa [76], intraclass correlation coefficient [77]) will be calculated and plausibility (eg, considering range and distribution) will be checked to minimize errors caused by data evaluation and entry.

Because of expected large dropout rate, which can lead to a critical amount of missing data, 2 separate analysis sets are planned: an intention-to-treat analysis and a per-protocol analysis. In the intention-to-treat analysis, all randomized participants regardless of protocol adherence will be included and missing data will be substituted by multiple imputation. Participants with sufficient attendance and adherence to the intervention as well as complete assessments of primary outcomes will be included in the per-protocol analysis, where missing data will not be considered.

Baseline values of participant characteristics will be compared between IG and CG using chi-square tests for categorical data, Mann-Whitney-U tests for nonparametric variables, and *t* tests for continuous and normally distributed parameters. For all normally distributed data (checked by Shapiro-Wilk test), mean and standard deviation will be calculated, and medians and interpercentile ranges will be calculated for not normally distributed data. Treatment effects will be analyzed using 2-factor ANOVA with repeated measurement. A 2-sided *P* value less or equal to .05 will be considered to indicate statistical significance. In addition, 95% confidence intervals and partial Eta² will be calculated. Changes in motor and cognitive function are possible mediators and moderators. These mediating and moderating effects on primary outcomes will be analyzed using multiple linear regression models. Additional explorative data analysis exceeding the proposed planned analyses will be performed. Depending on data structure, adequate analysis methods will be defined. These analyses aim to consider further influencing factors or subgroup analysis as well as the development of forecast models.

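### With 2:1 allocation, the repeated-measures ANOVA does not protect intention-to-treat P values and confidence intervals if the programme changes the spread of change scores; an unequal-variance test would, at almost no cost

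*Protocol article*

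**What the plan says.** The Statistical Analysis section of the protocol article fixes the test and the threshold: "Treatment effects will be analyzed using 2-factor ANOVA with repeated measurement", and "A 2-sided *P* value less or equal to .05 will be considered to indicate statistical significance". It also plans 95% confidence intervals. No unequal-variance alternative is named. The one distributional check, Shapiro-Wilk, concerns normality and decides how variables are described.

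The Study Design section sets "an allocation ratio of 2:1 for intervention (IG) and control group (CG), respectively". The Sample Size section works with a "small effect size (ɳ²=0.01, d=0.2"), "power of .80 (1-β), and 2 groups and 2 measurements", and arrives at 100 participants per group. The Dropout section then makes the arms unequal: "Hence, we decided to double the sample of IG to ensure the required sample of 100 participants in this group". It concludes: "Hence, a total sample size of 405 participants is required".

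Two analysis sets are planned. For intention to treat, "all randomized participants regardless of protocol adherence will be included and missing data will be substituted by multiple imputation", so the randomised ratio is kept. The per-protocol set keeps only participants with sufficient attendance and adherence and complete primary assessments, so its ratio may be closer to 1:1.

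**The concern.** With two measurements, the interaction F in a 2x2 repeated-measures ANOVA is the square of the pooled-variance t statistic on change. With equal arms, the pooled standard error is close to correct even if the arms differ in variance. With 2:1 arms it is not. The pooled variance is dominated by the larger arm, while the true variance of the difference depends more on the smaller arm. A larger trial at the same ratio does not help.

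The sample size was derived for the protected case, and the test was kept after the design left it. If the programme changes how much participants' change scores vary, as well as or instead of the mean, the reported standard error for the mean difference is wrong. It is too small if controls vary more and too large if the intervention arm varies more. The first makes false positives more frequent; the second costs power. The same test is planned for every primary and secondary outcome.

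**Working it through.** **Inputs.** From the article: two-sided 5%, 80% power, 100 per group, a 35% dropout allowance, 405 enrolled at 2:1. Assumed, because the article gives no figure: the ratio r of the variance of change (intervention / control), and a baseline-to-post correlation of 0.5 for the first step.

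**The plan's own figure.** With f = 0.1 (from η² = 0.01), N = 200 and correlation 0.5, the noncentrality is 0.01 × 200 × 2 / 0.5 = 8 and power is 0.804; N = 198 gives 0.7997. So 200 is reproduced, as an equal-arm calculation. The article's inflation is 200 × 1.35 = 270, or 135 per arm. Doubling the intervention arm gives 270 + 135 = 405.

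**True level at 2:1.** For large samples with n₁ = 2n₂,

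true variance / pooled variance = (r + 2) / (2r + 1),

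and the level of a nominal 5% test is 2[1 − Φ(1.96 / √that ratio)].

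| r (IG/CG) | True/pooled variance | Effective critical value | True level |
|---|---|---|---|
| 0.5 | 2.5/2 = 1.25 | 1.753 | 8.0% |
| 0.8 | 2.8/2.6 = 1.077 | 1.889 | 5.9% |
| 1 | 1 | 1.960 | 5.0% |
| 1.25 | 3.25/3.5 = 0.929 | 2.034 | 4.2% |
| 2 | 4/5 = 0.80 | 2.191 | 2.8% |

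The reported standard error is 1/√1.25 = 0.894 of the true one at r = 0.5 (11% too small) and 1/√0.80 = 1.118 at r = 2 (12% too large).

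**Simulation.** With 400,000 replicates at 270:135, the pooled test rejected in 7.98% (r = 0.5) and 2.85% (r = 2). Welch's test stayed between 4.95% and 5.03% in every scenario at that split. At 176:88 (65% of each arm) the formula gives the same levels. At 100:100 and 135:135 the pooled test stays at 5.0%.

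**Per-protocol set.** If low adherence brings the intervention arm down to 100 while controls number 135 × 0.65 ≈ 88, a two-fold variance ratio gives only 4.5% to 5.5%.

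**What uneven attendance would do.** Suppose half the intervention arm benefits by k standard deviations of change, the rest not at all, and benefit is unrelated to other variation. Then r = 1 + k²/4.

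- k = 0.4 (mean effect 0.2 SD): r = 1.04, level 4.9%.
- k = 0.8 (mean effect 0.4 SD of change, which is what 100 per arm detects with 0.807 power): r = 1.16, level 4.5%.
- r = 2 needs k = 2, a mean effect of 1 SD of change.

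**Cost in power on the conservative side.** An effect with 80% power under a correct standard error has Φ(2.80 − 2.01) ≈ 79% at r = 1.16 and Φ(2.80 − 2.19) ≈ 73% at r = 2.

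**The case against.** The strongest reply is that nothing in the article shows the variances to differ, so this could be said of any 2:1 trial analysed by ANOVA. Much of that stands. A reader might infer from the table that the trial's real false-positive rate is 8%. The documents do not support that, for three reasons.

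- Participants are allocated individually with a random element. If the programme affects nobody, both arms share one distribution of change and the level is 5.0%. An 8% level needs a programme with no mean effect that also halves the variance of change relative to controls.
- It is tempting to argue that controls vary more because they decline untreated. They are not untreated: the Intervention section has conventional treatment continue in both arms. The programme could narrow the spread by helping most those who would decline most, but the article does not say so.
- The mechanism that the article does suggest, varying attendance and response among those offered the programme, widens the intervention arm. That makes the test conservative, and only by about half a percentage point at the effect sizes planned for.

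It can also be said that variance handling belongs in an analysis plan that is not shown. That would answer a complaint about missing detail. Here the article names the test, and the named test is the one that loses its robustness under the allocation chosen.

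**Conclusion.** The point holds as a conditional weakness of low severity. For the intention-to-treat comparison at about 270:135, the chosen test gives correct standard errors only if the two arms have equal variance of change, and the 2:1 design removes the protection that equal arms would have given. The consequence is modest for r between 0.8 and 1.25 (5.9% to 4.2%) and material only near a two-fold ratio (8.0% to 2.8%); both ranges are assumptions. The likelier direction, from what the article describes, is intervals slightly too wide and a little lost power. The per-protocol comparison is hardly affected if its arms end near 1:1. No figure in the article is shown to be wrong by this point.

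**What to change.** In the Statistical Analysis section, replace the repeated-measures ANOVA for treatment effects with a comparison of change between arms that allows unequal variances: Welch's test, or a model for change with a separate residual variance in each arm. Take the 95% confidence interval from the same model. In the intention-to-treat analysis, apply it within each imputed data set and combine the estimates and standard errors across imputations.

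The point estimate remains the difference in mean change, so it does not move. A baseline-adjusted regression with robust standard errors would be a different estimator and a separate decision. The cost is a change of wording: no new data, and a negligible loss of power if the variances are in fact equal.

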### Outcomes

#### Determination of Outcomes

Primary outcomes refer to the motor qualities balance, mobility, and gait. Secondary outcomes are other motor variables such as strength and function of lower limbs and ADL as well as cognitive variables assessing overall cognition, language, processing speed, learning and memory, and visual spatial cognition. All outcome parameters are listed in Table 2. The aim of this study is to investigate changes in outcomes between IG and CG. Furthermore, the focus is on differences in all outcome variables between baseline and 16-week postassessment.

**Table 2 table2:** Primary and secondary outcome parameters.

	Outcome	Assessments (at baseline and 16-week postassessment)

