**Primary outcomes**		
	Balance	Frailty and Injuries: Cooperative Studies of Intervention Techniques 4 (FICSIT-4) [51]
	Mobility	
		Timed Up and Go test [52]
		6-meter walk test [53]
	Gait	Gait analysis using GAITRite: temporal and spatial gait parameters (gait speed, cadence, cycle time, step length, step width, gait variability, single support, and double support)
		- Walking with normal speed
		- Walking with normal speed and the task counting backwards from 50
		- Walking with normal speed and the task naming animals

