#### Primary Outcomes

Static balance will be determined using the Frailty and Injuries: Cooperative Studies of Intervention Techniques 4 scale (FICSIT-4) [51]. Mobility will be assessed using the timed Up and Go test [52] and 6-meter walk test [53]. The 6-meter walk test aims to capture normal gait speed. To reduce bias caused by the testing situation, participants are not explicitly informed about time keeping.

Temporal and spatial gait parameters will be analyzed using the electronic gait analysis system GAITRite (CIR Systems Inc, Franklin, NJ) with an active length of 4.88 meters, a spatial resolution of 1.27 centimeters, and a scan rate of 120 hertz. The following parameters are of special interest: gait speed, cadence, cycle time, step length, step width, gait variability, single support, and double support (as percentage of cycle time). Gait parameters are recorded for 3 different conditions: walking with normal speed, walking with normal speed and the task of counting backwards from 50, and walking with normal speed and the task of naming animals.

Changes in gait parameters caused by dual task will be calculated using the equation seen in Figure 3. The generated value represents dual-task costs indicating the better performance under dual-task condition the lower this value is [66,67].

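### The protocol labels 27 variables primary and sets one unadjusted .05 threshold, while the sample size is for a single test at .05

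*Protocol article*

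**What the plan says.** Under Determination of Outcomes the protocol states: "Primary outcomes refer to the motor qualities balance, mobility, and gait". Table 2 and the Primary Outcomes section then fill in these three qualities:

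- **Balance:** FICSIT-4.
- **Mobility:** Timed Up and Go and the 6-meter walk test.
- **Gait:** Table 2 has "Gait analysis using GAITRite: temporal and spatial gait parameters", and the text adds: "The following parameters are of special interest: gait speed, cadence, cycle time, step length, step width, gait variability, single support, and double support". It also says: "Gait parameters are recorded for 3 different conditions" (normal walking, walking while counting backwards, walking while naming animals).
- **Dual-task costs**, described in the same section: "Changes in gait parameters caused by dual task will be calculated using the equation seen in Figure 3".

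The Statistical Analysis section names a two-factor repeated-measures ANOVA for treatment effects and gives one decision rule, a two-sided P "value less or equal to .05 will be considered to indicate statistical significance". It plans an intention-to-treat and a per-protocol analysis. The Sample Size section uses a small effect (d=0.2), two-sided .05 and 80% power, and arrives at 100 analysable participants per group.

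**The concern.** The threshold and the sample size both fit a trial with one primary test. The outcome list does not. Every gait parameter in every walking condition carries the same primary label as FICSIT-4 and is held to the same .05. Normal gait speed appears twice, because the 6-meter walk is meant to capture it and GAITRite measures it again.

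At stake is whether a positive primary result can be called confirmatory. The Discussion makes publication of the program as a manual, and its permanent use in care facilities, depend on the program proving effective. If one favourable parameter among 27 could support that conclusion, the nominal 5% error rate would not describe it.

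**Working it through.** **The plan's own figure.** For the within-between interaction with two groups and two measurements, λ = f²·N·m/(1−ρ), with 1 and N−2 degrees of freedom. Inputs from Sample Size: f = d/2 = 0.10, m = 2, α = .05, power .80. The correlation ρ between measurements is not given, so 0.5 is assumed. At N = 200, λ = 0.01 × 200 × 2 / 0.5 = 8.0 and power is 80.4%. The smallest N with 80% power is 199, or 200 with equal groups. The stated 200 therefore reproduces, for exactly one test at .05. Other values of ρ do not reproduce it: 0, 0.3 and 0.7 give 395, 277 and 120.

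**Count of primary variables** (Table 2 and Primary Outcomes):
- balance 1 + mobility 2 + gait 8 × 3 = 24, in total 27
- dual-task costs add up to 8 × 2 = 16, making 43
- the second analysis set is not counted here

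**Chance of at least one P ≤ .05 when there is no effect on any variable.** Under independence it is 1 − 0.95^k. For correlated tests, an equicorrelated normal model was integrated numerically. The documents give no correlations, so r is an assumed range.

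| Tests | Independent | r=0.3 | r=0.5 | r=0.7 | r=0.8 | r=0.9 |
|---|---|---|---|---|---|---|
| 27 (as listed) | 75% | 63% | 48% | 33% | 25% | 17% |
| 43 (with dual-task costs) | 89% | 77% | 59% | 38% | 29% | 19% |
| 3 (one per domain) | 14% | 14% | 13% | 11% | 10% | 8% |

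A more structured assumption sets correlations of 0.3–0.7 between gait parameters and 0.7–0.9 between walking conditions. It gives about 41–61% for the 27 variables.

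**The opposite reading, that all three domains must succeed.** With one test per domain at exactly 80% power, joint power is 0.8³ = 51% if independent, rising to 66% at r = 0.7. The planned 80% does not describe this reading either.

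**Power after adjustment** (f = 0.10, ρ = 0.5, equivalent to a difference in change of 0.4 SD):
- 100 per group: 80% at .05; 66% at .05/3 = .0167, the first Holm step; 37% at .05/27 = .00185.
- 175/88 analysed (270 × 0.65 and 135 × 0.65, the 2:1 split of 405 less the assumed 35%): λ = 0.16 × 175 × 88 / 263 = 9.37, giving 86% at .05 and 74% at .0167.

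**The case against.** The strongest reply is that a protocol article commonly leaves the multiplicity procedure and the success rule to an analysis plan, which is not shown here. That is fair: the lack of a success rule is not itself the finding. What stands is what the article does fix, namely the primary label on 27 variables, an unadjusted .05, and a sample size for one test. The article also sets its exploratory analyses apart as going beyond the planned ones, so the listed gait parameters cannot be treated as exploratory by default.

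Three stronger readings are tempting, and the documents do not support them.

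- A reader might infer that the trial will be declared positive if any one of the 27 is significant. The threshold sentence defines statistical significance in general and does not say this. The error rates above are conditional on that reading.
- A reader might take 75%, or 89% with dual-task costs, as the actual error rate. Both need independence. Cycle time is essentially the inverse of cadence, gait speed is step length times cadence, the same people walk under three conditions, and dual-task costs are computed from the same parameters. Nor is 33% a floor, since higher correlations give 25% or 17%.
- A reader might conclude that almost any data set would yield a significant primary outcome. At r = 0.7 about two of three null data sets would yield none.

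One could also say that the protocol has three primary outcomes, not 27. On that reading the inflation is smaller, 8–14%, but still above 5%. The article does not say which variable represents mobility or gait.

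**Conclusion.** The point holds in a conditional form. The plan fixes a rule that does not control the error rate over its own primary list, and its sample size belongs to a single test. If no variable is truly affected and one significant primary variable is read as success, the false-positive chance is about 63% to 33% for assumed common correlations of 0.3 to 0.7, and still 17% at 0.9. The conclusion that the rate exceeds 5% does not depend on the exact correlation; the size does. This should be corrected, because it decides whether the primary conclusion can be confirmatory.

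**What to change.** Before outcome data are analysed by group, document an amendment that:

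1. names one primary measure per domain, for example FICSIT-4 for balance, Timed Up and Go for mobility and single-task GAITRite gait speed for gait;
2. controls the family-wise error at .05 over the three, for example with Holm or a fixed sequence;
3. limits any confirmatory claim to the domains that pass;
4. moves the remaining gait parameters, the dual-task conditions, the dual-task costs and the 6-meter walk test to secondary or exploratory status.

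No new data are needed. Enrollment began in May 2015, however, so this is a change during conduct and must be dated and reported as such. The statistical cost with Holm is power at the first step: from about 80% to 66% at the protocol's target of 100 per group, or from 86% to 74% at 175/88. A fixed sequence keeps about 80% for the first domain at 100 per group, but each later domain can be tested only if those before it pass. Restate the power for the chosen procedure rather than enrolling more participants.
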